# HEALTH ECONOMICS

Health economics will be analyzed with respect to Swedish conditions first and with an international perspective.

DIRECT COSTS

To evaluate healthcare costs, the internal accounting and billing systems within hospitals will be utilized to estimate direct costs based on Cost Per Patient (CPP) principles for individual treatments and/or Diagnosis-Related Groups (DRG) for surgery and fertility treatment. We will also obtain CPP and/or DRG-based cost data from the hospitals where the included women receive care in connection with surgery, fertility treatments, pregnancy, childbirth, and postpartum follow-up. In addition, data on employment status at baseline will be collected. Quality-Adjusted Life Years (QALY) will be computed using data from the EQ-5D instrument. Variations in changes to health status and quality of life will be utilized for a cost-utility analysis, with the results presented as an Incremental Cost-Effectiveness Ratio (ICER). This analysis will provide insights into the additional cost per year of full health achieved with first line surgery compared to first line ART.

INDIRECT COSTS

To assess indirect costs related to the disease, both study arms will be examined with regard to estimating productivity costs, specifically the level of decline in production. Methods such as the friction cost method may be employed for this purpose.

# ADENOMYOSIS

The presence of suspected adenomyosis, on ultrasound and/or MRI, will be recorded and described at baseline according to Morphological Uterus Sonographic Assessment (MUSA) (26, 27). The presence of adenomyosis will not affect allocation but will be used at the end of the study in the interpretation of the findings, as a sub-group analysis.

# OBSTETRICAL OUTCOMES

Obstetrical outcomes and complications will be collected from patient journals and from the National Pregnancy register: Obstetrical outcomes (gestational age at the delivery, birth weight, umbilical artery and vein blood analysis, neonatal complications within 7 days after delivery, and complications (pregnancy-related complications (premature delivery, preeclampsia, gestational diabetes, placenta previa, placenta abruptio, placenta spectrum disorders, bleeding complications during pregnancy); delivery-related complications (instrumental delivery, emergency caesarean section, pelvic floor trauma, delivery related bleeding, manual placenta removal); complications within 8 weeks postpartum (infection (endometritis, pelvic inflammatory disease, urinary tract infection, wound infection, sepsis), remaining conceptual tissue with and without surgical intervention, use of analgesics). In case of missing information women will be contacted by phone for additional information.

The power calculation was conducted for the primary outcome, hence, there may be insufficient power to compare pregnancy complications due to the small proportion of complications and the fact that all participants will not experience a complete pregnancy. To better assess pregnancy complications, we will compare the study population with the broader population of pregnant women. In addition to the comparison between the two randomized groups the whole study population will be compared with women giving birth during the time the study is running with a diagnosis of endometriosis and no surgical treatment. To identify the control group, data from the Patient Register (including outpatient and inpatient diagnoses) and the Swedish National Quality Register of Gynecological Surgery (Gynop) will be linked with the National Pregnancy Register (2025 to the study's end). Pregnancies complicated by endometriosis stage III-IV and surgery treatment will be compared with those with endometriosis and no surgical treatment as well as a comparison with women without endometriosis. Although undiagnosed endometriosis in the pregnant population poses a challenge in creating a control group free of endometriosis or with a specific stage of endometriosis, linking the gynaecological operation and register with diagnosis will allow the creation of control groups with largely correct status of endometriosis. Each control group is planned to include 1000 persons.

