# SYNOPSIS

| **Protocol Title** | First line surgery versus first line fertility treatment using assisted reproductive technologies in patients with advanced endometriosis: A national multicenter randomized controlled trial. |
| --- | --- |
| **Indication** | Patients with endometriosis AAGL stage III-IV eligible for their first fertility treatment |
| **Primary objective** | To assess whether surgery conducted prior to treatment with assisted reproductive technologies (ART) in patients with endometriosis AAGL stage III-IV increases cumulative live birth (CLBR) as compared to first line ART. |
| **Secondary**  **objectives** | To assess if surgery prior to ART treatments in women with endometriosis AAGL stage III-IV result in improved, Cumulative Pregnancy Rate (CPR) and lower miscarriage rate as compared to first line ART.  To compare time to CLBR and CPR  To evaluate intra- and postoperative complications after oocyte pick-up and surgery.  To compare quality of life and pain at follow up and do a health economic evaluation.  To examine obstetrical outcomes of the resulting pregnancies  To investigate differences in plasma progesterone levels (P-progesterone) at the day of frozen embryo transfer in hormone replacement therapy (HRT) cycles |
| **Study Design** | Randomized controlled trial |
| **Planned sample**  **Size** | 350 |
| **Inclusion criteria** | - Age 18 - 38 years. - Endometriosis AAGL stage III-IV - Eligible for ART-treatment such as in vitro fertilization (IVF) or intracytoplasmic sperm injection (ICSI) - Body mass index 18 – 35 kg/m^2^ |
| **Exclusion criteria** | - Previous surgery for endometriosis except diagnostic laparoscopy. - Previous IVF/ICSI cycles - Hemato- /hydrosalpinx - Clear indication for surgery such as ureteral stenosis or intestinal sub-occlusive symptoms - Suspicion of ovarian malignancy - Submucosal fibroids of any size (FIGO 0-1) or intramural fibroids (FIGO 2-5) > 4 cm - Uterine malformations (U 1-6 according to ESHRE classification) - Contraindications to surgery - ART treatment with donated oocytes |
| **Primary outcome** | Cumulative live-birth rate (CLBR) within three years from first treatment (Surgery or ART) |

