# LONG-TERM FOLLOW-UP

There will be an opportunity for inclusion in a long-term follow-up, where participants from both the randomized controlled study and the cohort study will be eligible if they consent. In the long-term follow-up, conducted 10 years post-inclusion, we will utilize the unique Swedish personal identification number and gather data after study conclusion on infertility treatments from the National Register of ART in Sweden (Q-IVF) live births from the Swedish Medical Birth Register (MFR) and The National Pregnancy Register and number of recurrent endometriosis surgeries from Gynop. For details about variables collected from each register see appendix.

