| OFRIABEF | Åtgärd vid ofri. barnlöshet: assisterad befruktning |
| OFRIANN | Åtgärd vid ofri. barnlöshet: annan |
| OFRIBARN | Ofrivillig barnlöshet (år) |
| OFRIIATG | Åtgärd vid ofri. barnlöshet: ingen |
| OFRIICSI | Åtgärd vid ofri. barnlöshet: ICSI |
| OFRIKIRU | Åtgärd vid ofri. barnlöshet: kirurgi |
| OFRISTIM | Åtgärd vid ofri. barnlöshet: ovulation stimulering |
| PARITET | Paritet, barnets ordningsnummer |
| PARITET_F | Paritet, ordningsnummer för förlossning |
| PSTOPDAT | Upphört med p-piller |
| ROK0-ROK2 | Rökning 3 månader före / vid inskrivning till MHV / vecka 30-32 |
| SECAVSL | Förlossningen avslutas med kejsarsnitt |
| SECFORE | Förlossningen startas med kejsarsnitt |
| SECMARK | Kejsarsnitt, markering |
| SECTIO | Sectio- elektivt eller ej elektivt |
| SFINKTER | Bristningar - sfinkter |
| SMDAT | Senaste menstruation |
| SNUS0-SNUS2 | Snusning 3 månader före / vid inskrivning till MHV / vecka 30-32 |
| SPUTDAT | Spiral uttagen |
| SUGKLOCK | Förlossningen avslutas med sugklocka |
| TANG | Förlossningen avslutas med tång |
| TID7DOD | Antal döda barn inom 0-6 dygn |
| TIDDODF | Antal dödfödda barn |
| TIDLEVF | Antal levande födda barn |
| TIDSDOD | Antal senare döda barn |
| TIDSPOAB | Antal tidigare spontan abort |
| TIDXGRAV | Antal X-graviditeter |
| TSECAR | Tidigare sectio, år |
| TSECTIO | Tidigare sectio |
| VAGINAL | Förlossningen avslutas vaginalt |

[figure not shown]

[figure not shown]

[figure not shown]

[figure not shown]

[figure not shown]

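### Register controls for obstetric outcomes ignore mode of conception and do not exclude trial participants, so a difference cannot be attributed to endometriosis or surgery

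*Protocol*

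**What the plan says.** The OBSTETRICAL OUTCOMES section of the protocol notes that the trial was sized for the primary outcome and may lack power for pregnancy complications. Its answer is: "To better assess pregnancy complications, we will compare the study population with the broader population of pregnant women". Beyond the comparison of the randomized arms, it sets up these contrasts:

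- All trial women against unoperated women with diagnosed endometriosis: "the whole study population will be compared with women giving birth during the time the study is running with a diagnosis of endometriosis", with the added condition of no surgical treatment.
- Operated advanced disease against unoperated endometriosis: "Pregnancies complicated by endometriosis stage III-IV and surgery treatment will be compared with those with endometriosis and no surgical treatment".
- A further contrast, "as well as a comparison with women without endometriosis".

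Controls are found by linking the Patient Register and Gynop to the National Pregnancy Register, from 2025 to the end of the study, with 1000 persons per group. The section discusses one threat to validity, undiagnosed endometriosis among controls. It does not mention mode of conception, and it does not say that trial participants are removed from the pools.

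Three other parts of the protocol bear on this:

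- STUDY ENROLLMENT admits only women referred or eligible for ART and excludes earlier endometriosis surgery other than diagnostic laparoscopy. STUDY TREATMENT plans ART in both arms.
- The Covariates paragraph of STATISTICAL CONSIDERATIONS adjusts primary and secondary outcomes for age, BMI, AMH, ART type and center.
- The Medical Birth Register (MFR) list in the APPENDIX includes a variable for assisted conception, "Åtgärd vid ofri. barnlöshet: assisterad befruktning".

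**The concern.** The two sides of the register comparison differ in mode of conception by construction. Trial women are selected because they are candidates for ART. The controls are selected from all births, with or without an endometriosis diagnosis. If ART conception is itself related to complications such as preeclampsia, placenta previa or preterm delivery, that relation enters the comparison in full and cannot be told apart from an effect of endometriosis or of surgery.

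The second defect needs no outside assumption. A woman treated only in the ART arm has diagnosed endometriosis and no endometriosis surgery. If she gives birth in the window, she satisfies the control definition. In the first contrast she is also part of the trial group, so she can stand on both sides.

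At stake is the interpretation of a supplementary analysis that the protocol offers as its remedy for low power on complications.

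**Working it through.** **Definitions side by side**

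| Feature | Trial women | Register controls |
| --- | --- | --- |
| ART candidacy | Required | Not a criterion |
| Endometriosis | AAGL stage III-IV | Any diagnosis, or none |
| Endometriosis surgery | None before entry; planned in one arm | None, in the endometriosis control group |
| Trial participation | Yes | Not excluded |

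**Does the stated covariate list repair this?** Age and BMI could be carried over to a register comparison. ART type could not: STUDY OBJECTIVES defines it as IVF or ICSI, so it has no value for a birth without ART. AMH is not among the MFR or Patient Register variables listed in the appendix, and trial center has no meaning for a register control. The list fits the randomized comparison. The confounder adjustment under PROSPECTIVE COHORT STUDY concerns the parallel cohort.

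**Overlap.** The inputs are the planned 350 participants, hence 175 per arm, and the assumed live birth rate of 55% in the ART-only group, both from the power calculation.

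175 × 0.55 = 96.25, or about 96 women.

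This is a ceiling on eligibility. It assumes that none of these women later has endometriosis surgery, and it is not the number expected in a sample of 1000, which depends on a pool size that the documents do not give. If all 96 were drawn, they would be 96 / 1000 = 9.6% of that control group.

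**Confounding.** The documents give neither the effect of ART on complications nor the share of ART births on either side. The following inputs are assumptions, used only to show a range:

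- R, the risk ratio for ART against non-ART conception: 1.25 to 2.
- pS, the ART share among trial births: 70% to 100%.
- pC, the ART share among control births: 5% to 40%.

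With no true effect of endometriosis or surgery, the apparent risk ratio is

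(1 + pS(R − 1)) / (1 + pC(R − 1)).

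- Mild end (R = 1.25, pS = 70%, pC = 40%): 1.175 / 1.10 = 1.07.
- Middle (R = 1.5, pS = 85%, pC = 20%): 1.425 / 1.10 = 1.30.
- Strong end (R = 2, pS = 100%, pC = 5%): 2.00 / 1.05 = 1.90.

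If the ART share is equal on both sides (pS = pC), the factor is 1.00 whatever R is.

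**A remedy that would overshoot.** STUDY OBJECTIVES counts spontaneous pregnancies as a secondary outcome, so some trial births will not follow ART. Restricting only the controls to IVF/ICSI births reverses the mismatch. With R = 2, pS = 70% and pC = 100%, the ratio under no effect is 1.7 / 2.0 = 0.85. Conception mode therefore has to be handled on both sides.

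**The case against.** The best counter-argument is that the details of a supplementary register comparison normally belong in the statistical analysis plan, which is not at hand. That plan may adjust for conception mode, and the assisted-conception variable in the MFR list suggests that the data could be obtained. The Pregnancy Register variable list is not shown and cannot be judged. This stands as far as regression adjustment goes. It does not cover the control definition, the linkage sources and the group size, which are fixed in the protocol and determine which women are extracted. If 5% to 40% of controls conceived by ART (assumed), only about 50 to 400 of 1000 would be comparable on this point, so adjustment after extraction would have little to work with.

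A reader might infer more than the documents support:

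- **That the obstetric objective cannot be answered.** The objective in STUDY OBJECTIVES compares surgery before ART with first line ART. The randomized comparison addresses that, and the register comparison is expressly additional.
- **That the comparison measures ART as much as endometriosis or surgery.** No figure in the documents supports such a weighting. At the mild end of the assumed range the distortion is only 1.07.
- **That no adjustment is stated at all.** Age and BMI are in the covariate list for secondary outcomes, and obstetric outcomes are listed among these.
- **That 96 participants will sit among the controls.** This is the eligibility ceiling. In the contrast of operated with unoperated women, ART-arm participants belong in the unoperated group without being counted twice. In the contrast with all trial women, shared members would dilute a difference rather than create one.

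The protocol may also legitimately want the general birth population as a reference. As description, that comparison can stay.

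**Conclusion.** The point holds for the supplementary register comparison only. As the protocol defines it, a difference between trial women and register controls cannot be attributed to endometriosis or surgery rather than to conception mode, and participants treated only in the ART arm can appear on both sides of the contrast that uses all trial women.

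Both defects follow from the protocol's own definitions. The overlap ceiling rests on the planning figures. The size of the confounding is not known from the documents: the range of about 1.07 to 1.90 rests wholly on the assumed ART shares and risk ratios, and its upward direction on the assumption that ART raises risk. The randomized obstetric comparison and the primary endpoint are unaffected.

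**What to change.** Amend the OBSTETRICAL OUTCOMES section in three places:

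1. Exclude participants of the trial and of the parallel cohort from the register control pools.
2. Match controls to trial births on mode of conception (IVF/ICSI or spontaneous), or stratify or adjust for it on both sides. Take it from the MFR assisted-conception variables already listed or from Q-IVF, which is already planned for the long-term follow-up. Include maternal age, parity and BMI in the same step, for which the MFR list has age, parity, height and weight. Treat plurality as a sensitivity analysis, because it may itself be a consequence of the treatment.
3. Keep the comparison with the unrestricted birth population and label it descriptive.

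The cost is small: protocol wording and one more register variable or linkage. The downside is that the unoperated endometriosis group may yield fewer than 1000 matched controls. The documents do not allow a reliable count, so the target should be reviewed once the size of the pool is known.

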# PROSPECTIVE COHORT STUDY

For patients who decline participation in randomization or are excluded after randomization, an option to be included in an observational prospective cohort study will be provided. Participants in this study will adhere to the same study protocol as in the RCT, except for the randomization itself. Analyses for this cohort will adjust for confounding factors using regression models, as described in the statistical methods section.

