An earlier meta-analysis found that the number of oocytes and fertilization rates are lower in women with endometriosis as compared to those without, although not necessarily impacting the live birth rate (12). Still, some previous studies have shown lower likelihood of live birth and pregnancy after in vitro fertilization (IVF) in women with endometriosis compared to women with unexplained or tubal infertility (13, 14). Even though there is some controversy when it comes to the evidence of association between endometriosis and adverse reproductive outcome after IVF, there is biological plausibility for this type of association, especially in women with advanced endometriosis (chronic inflammation affecting folliculogenesis, technical difficulties at oocyte retrieval due to endometriomas or adhesions, increased risk of pelvic infection after oocyte pick-up) (15, 16).

RATIONALE FOR STUDY

Only a few comparative retrospective studies on first-line surgery versus first-line ART have been performed, with no available randomized controlled trials (RCTs) (17). In two retrospective register studies, first-line surgery in patients with deep endometriosis (DE) in the anterior compartment or colorectal DE showed improved live birth rates (LBR) and pregnancy rates (PR) compared to first-line ART (18, 19). An important limitation in the previous studies on patients with endometriosis has been the challenge of staging and characterizing the disease consistently using preoperative imaging techniques. Currently, the decision regarding the choice between surgery and IVF is collaborative and individualized, considering various factors such as the patient's medical and surgical history, presence of pain symptoms, age, results of ovarian reserve testing, and semen analysis. Lack of randomized RCTs or at least robust prospective cohort studies comparing these two approaches is noteworthy. Hence, there is an obvious need for a randomized controlled trial to address the impact of surgery prior to ART on the reproductive outcomes in women with endometriosis AAGL stage III-IV, to help patients and health-care workers with decision-making, with the overall aim to improve patient-outcomes.

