- postpartum complications (defined as within 8 weeks postpartum): infections (endometritis, pelvic inflammatory disease, urinary tract infection, wound infection, sepsis), remaining conceptual tissue with and without surgical intervention, use of analgesics

COVARIATES

Potential covariates will be collected from patients’ medical records.

*Baseline characteristics:*

- Age (continuous and dichotomized as < and > 35 years)
- Infertility duration (months)
- Infertility due to social factors (yes/no)
- Infertility due to pain from endometriosis (yes/no)
- Infertility due to male factor (yes/no)
- Smoking (yes/no)
- Snuffing (yes/no)
- BMI (continuous)
- Hormonal endometriosis treatment (yes/no, if yes subtype of drug, duration of hormonal treatment prior to first surgery or ART)
- Parity (0, 1-2 or >2)
- previous caesarian sections (yes/no)
- previous abdominal surgery (yes/no)
- previous adnexal surgery (yes/no)
- previous uterine or cervical surgery (yes/no, type of surgery)
- smoking habits (yes/no)
- ovarian reserve (AMH<0.5ng/L, 0.5-3.5 ng/L and AMH >3.5ng/L)
- myoma (yes/no)
- time from randomization to first oocyte pick-up or surgery (depending on which treatment arm the patient is randomized to)
- ASA-class (1-2 or 3-4)
- Other diseases affecting the outcome: hypothyroidism, diabetes, bleeding disorders or thrombogenic diseases, hypertension, hyperprolactinemia

*Imaging specific data (Ultrasound MRI)*:

- #ENZIAN-score
- AAGL-score
- Adenomyosis (yes/no)
- antral follicle count (AFC)

*Perioperative data:*

- #ENZIAN score
- AAGL score
- EFI score
- Surgical procedure defined by KVÅ- codes: adnexal surgery (yes/no), surgery on deep endometriosis anterior compartment (yes/no) or deep endometriosis posterior compartment (yes/no)
- Colorectal surgery (yes/no, if yes rectal shaving, discoid resection or segmental resection)
- Urological surgery (yes/no, if yes bladder resection, reimplantation of ureter, end to end anastomose of ureter, shaving of ureter)
- Perioperative data: estimated blood loss, operative time, conversion rate
- Annual surgeon volume (number of advanced endometriosis surgeries per year)
- Cumulative surgeon volume (number of advance endometriosis surgeries in total at surgery)
- Consultant surgeon (yes/no, if yes which specialty)
- Reoperation (yes/no) until 2 months post-surgery
- Readmissions (yes/no) until 2 months post-surgery
- Hospital stays (days)
- Time to normal activity of daily life (ADL) (days)

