- Uterine malformations (class U1-U6 according to ESHRE/ESGE-classification) (30)
- Patients with contraindications to surgery
- Patients undergoing ART with donated oocytes

RANDOMIZATION

After verification of eligibility, signed informed written consent participants will be randomly assigned to either undergo first-line ART or first-line surgery, followed by ART by equal allocation, 1:1. The randomization procedure will be stratified for participating center (permuted block design). Randomization will be performed at each site using the web-based instrument Red Cap. All inclusion criteria and no exclusion criteria must be met. One month before first treatment (IVF or surgery), inclusion and exclusion criteria are entered into the randomization/registration application RedCap. Patients withdrawn from the study after randomization but before treatment will be substituted by newly enrolled patients. Patients withdrawn from the study after first treatment will not be substituted. Username and password are required to log in; each investigator authorized to register patients has a personal login username and password. If all criteria are met, patients are registered, and the allocated patient number is recorded in the patients’ medical file.

There could be some uncertainty surrounding participants' willingness to engage in a Randomized Controlled Trial (RCT) comparing two fundamentally distinct approaches. Therefore, we intend to offer women who fulfill eligibility criteria but decline randomization the opportunity to take part in a parallel study – a prospective cohort study, that would provide valuable real-world outcomes of two different approaches to treatment of endometriosis -associated infertility. This parallel study will evaluate identical outcomes to those in the randomized trial. However, instead of random assignment, participation decisions will be made by the patients themselves, resulting in what is commonly referred to as a patient preference trial.

DEFINITION START OF TRIAL

Start of trial will be defined as start of first treatment which will be either surgery or first ART cycle (e.g start of FSH injections).

DEFINITION END OF TRIAL

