**Primary analysis**

The primary analysis will compare proportions between treatment groups and report the crude relative risk (RR) with 95% confidence intervals. Adjusted analyses will use log-binomial regression (or modified Poisson with robust variance if convergence fails), including prespecified covariates (age, BMI, AMH, ART type, center). A two-sided α=0.05 will be used.

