**Additional analysis**

– Exploratory subgroup analyses will not be adjusted for multiplicity.

– Safety outcomes will be summarized descriptively by treatment group (frequency, severity, relation to treatment).
– All available data will be used, including outliers.
– Missing outcome data will be handled under the missing-at-random assumption via maximum likelihood in mixed models; for regression models requiring complete covariates, complete-case analysis will be applied.

Covariates

Primary and secondary outcomes will be adjusted for prespecified covariates (age, BMI, AMH, ART type, center), chosen based on clinical relevance and prior evidence.

POWER CALCULATION AND SAMPLE SIZE

The sample size calculation was based on a two-sample comparison of proportions with a two-sided α=0.05 and 80% power. Based on observational data (18, 19), the cumulative live birth rate (CLBR) after three IVF cycles was assumed to be 55% in the ART-only group and 71% in the surgery+ART group (relative risk ≈1.29). This yields a required sample size of 142 participants per arm (284 total). Allowing for 20% attrition, the planned total sample size is 350 participants.

The necessary sample size for this study is estimated to 323 patients to accommodate a statistical analysis method. This estimation uses the 'pwr' package in R, specifically employing the power.prop.test method, which is designed to compare two proportions. This method is more aligned with contemporary statistical practices and provides a clear, transparent methodology for determining the required sample size based on expected success rates.

This means inclusion of 29 patients from/each center/year and 15 surgeries/year. In a Swedish study published in 2022 the prevalence of endometriosis in patients referred for ART-treatment was 21.8% and 17.2% of women had DE (14). In 2021 almost 10 500 IVF cycles were performed in Sweden, while more than 5 500 of those were first-time IVF/ICSI with autologous gametes ((46) Figure 22).

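### The preference cohort's confounder adjustment is referred to a section whose only full covariate list was set for the randomised comparison, and that list omits pain and medical/surgical history

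*Protocol*

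**What the plan says.** The protocol plans a parallel cohort for eligible women who decline randomisation (*Study Enrollment*, Randomization). There, "instead of random assignment, participation decisions will be made by the patients themselves". The same paragraph adds: "This parallel study will evaluate identical outcomes to those in the randomized trial". The section *Prospective Cohort Study* also admits women excluded after randomisation, and gives the analysis in one sentence: "Analyses for this cohort will adjust for confounding factors using regression models, as described in the statistical methods section".

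*Statistical Considerations* defines the exposure as the randomised allocation and does not mention the cohort. Its Primary analysis paragraph fits a regression "including prespecified covariates (age, BMI, AMH, ART type, center"). Its Covariates paragraph states: "Primary and secondary outcomes will be adjusted for prespecified covariates (age, BMI, AMH, ART type, center), chosen based on clinical relevance and prior evidence". The quality-of-life and pain models use the same list without ART type.

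The rationale (*Why This Trial Is Needed*) describes how the choice between surgery and IVF is currently made: "considering various factors such as the patient's medical and surgical history, presence of pain symptoms, age, results of ovarian reserve testing, and semen analysis".

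A wider set of variables is recorded under *Study Objectives*, Covariates, introduced by: "Potential covariates will be collected from patients’ medical records". It includes pain-related and male-factor infertility, previous abdominal and adnexal surgery, other diseases, AAGL and #ENZIAN scores, and adenomyosis. That paragraph assigns none of them to a model.

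**The concern.** In the randomised trial, allocation balances prognostic factors in expectation, and a short covariate list mainly adds precision. In a cohort where patients choose, covariate adjustment is the only protection against bias. A list that suffices for the first purpose need not suffice for the second.

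The cohort sentence points to a place that holds a list built for the first purpose. An analyst following the text would compare surgery choosers with ART choosers without adjusting for pain or for medical and surgical history. The protocol itself names both as considerations in that choice. The cohort is presented as real-world evidence on the same two strategies with the same outcomes, so its estimate will be read beside the trial result. If the set is settled only after outcomes are known, confounder selection could also become data-driven.

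**Working it through.** **1. Where the cross-reference leads.** The cohort section points to the statistical section. The only full list there is age, BMI, AMH, ART type and center. It is applied to primary and secondary outcomes, and the cohort has the trial's outcomes. The natural reading is that this list carries over. If the reference means only the type of regression model, it leads to no confounder set at all.

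**2. Named drivers of choice against the list.**

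| Driver named in the rationale | In the five-covariate list? | Recorded at baseline? |
| --- | --- | --- |
| Age | Yes | Yes |
| Ovarian reserve | Yes (AMH) | Yes |
| Semen analysis | By proxy only (ART type) | Male-factor infertility, yes/no |
| Pain symptoms | No | Pain-related infertility, yes/no; NRS; EHP-30 |
| Medical and surgical history | No | Previous abdominal and adnexal surgery; other diseases |

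Two of five are adjusted for, one is covered by proxy, and two are absent. Disease extent (AAGL, #ENZIAN) is recorded and unadjusted, but the rationale does not name it as a driver.

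**3. ART type as a proxy.** The ART data list records the performed fertilisation method for each cycle, which comes after the treatment choice and, in the surgery group, after surgery. The background section says spontaneous pregnancies are frequent after surgery for deep disease. A woman who conceives before any ART cycle has no performed method. If ART type means the performed method, the complete-case rule for models needing complete covariates (*Additional analysis*) could drop such women, and more of them from the surgery group. The baseline male-factor item avoids this.

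**4. Possible size.** The documents give no effect, sample size or confounder prevalence for the cohort. The only reference figure is the trial's planning effect, 0.71/0.55 = 1.29, which matches the stated value. For one omitted yes/no factor with relative risk r for live birth, and prevalence p1 in surgery choosers and p0 in ART choosers, the estimated relative risk is multiplied by

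[1 + p1(r − 1)] / [1 + p0(r − 1)].

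All values of r, p1 and p0 below are assumptions.

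| r | p1 / p0 | Calculation | Factor |
| --- | --- | --- | --- |
| 0.9 | 0.6 / 0.4 | 0.94 / 0.96 | 0.98 |
| 0.7 | 0.8 / 0.2 | 0.76 / 0.94 | 0.81 |
| 1.2 | 0.6 / 0.4 | 1.12 / 1.08 | 1.04 |
| 1.3 | 0.8 / 0.2 | 1.24 / 1.06 | 1.17 |

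With no true effect, these factors are the relative risks that would be observed. The formula treats the omitted factor as independent of the covariates already in the model. Correlation with age, AMH or ART type would change these figures. Several omitted factors could reinforce or offset one another.

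**The case against.** The strongest reply is that the protocol does commit to adjusting for confounders and does collect the candidate variables. The cross-reference may concern the regression models only, and a final confounder list for a parallel observational study is commonly left to an analysis plan, which is not at hand. A reader might infer that the protocol restricts the cohort to the five covariates. It does not say so; that is a reading of three passages together. What stands is that the sentence does not defer to a later plan. It refers to a section of this document, and what is found there is either a list built for another purpose or no list.

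Eligibility also removes some confounding. Previous surgery for endometriosis (other than diagnostic laparoscopy) is excluded, as are clear indications for surgery such as ureteral stenosis, and disease is limited to AAGL stage III-IV. This holds for women who decline randomisation, and it narrows the gap. It does not cover pain, other medical and surgical history, or variation in stage and compartment within stage III-IV. The rationale describes routine practice, so carrying its drivers over to this restricted group is an assumption, though a reasonable one.

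A reader might also infer that the protocol names disease extent as a driver of choice. It does not. Extent is a plausible confounder on clinical grounds and is recorded, but the text does not support a stronger statement.

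**Conclusion.** The point holds in limited form. The cross-reference leads to no cohort-specific confounder set. Read as written, the adjustment leaves out two of the five drivers of choice that the protocol names and covers a third only by proxy.

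The cohort estimate is therefore open to residual confounding. A reader might go further and call the comparison biased by a known amount or in a known direction; the documents do not support that. The illustrative factors of 0.81 to 0.98 and 1.04 to 1.17 rest wholly on assumed prevalences and relative risks. They show that one omitted factor could matter beside a planning effect of 1.29, and no more.

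The point concerns the parallel cohort only. The randomised primary analysis and the trial's sample size are untouched. It should be corrected, but it does not threaten the trial's main conclusion.

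**What to change.** In *Prospective Cohort Study*, replace the cross-reference with a confounder set specific to the cohort, fixed before outcomes are examined and limited to pre-treatment variables already collected:

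- age, AMH, BMI, center, parity and infertility duration;
- male-factor, social and pain-related infertility, taken from the records;
- previous abdominal and adnexal surgery, and relevant other diseases;
- imaging-based AAGL and #ENZIAN findings, and adenomyosis.

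Use the baseline male-factor item instead of the performed ART type. Fit the set by regression or by a propensity score, with the number of terms suited to the cohort size actually reached, since none is stated.

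Baseline NRS and EHP-30 scores may be added only with a caveat. In the trial they are completed after the allocated treatment is known (*Patient Reported Outcomes*, Procedure); in the cohort they would follow the woman's own choice and could be influenced by it. The records-based pain item is the safer main adjustment variable.

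The cost is protocol wording, a larger model and possibly wider intervals. No new data collection is needed.
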